### Data collection instrument

To evaluate the effectiveness of the module and the acquisition of knowledge by the participants, a form developed in Google forms will be used, applied as a pre-test and post-test for both the control group and the experimental group.

The data collection forms will consist of two documents. The first is the registration form with demographic characterization, which will collect personal and academic information relevant to the study; while the second is a form that will be used as a pre- and post-test containing a problem situation made up of four objective questions focused on topics such as team motivation and engagement, organizational culture, conflict management and constructive feedback, in addition to the adaptation of the Nursing Student Self-Perception Questionnaire on Exercising Leadership (QUAPEEL), developed by Cardoso, Ramos and D’Innocenzo (2014) [11].

The problem situation is made up of six objective questions, and each question contains four alternative answers. The questions in the document are: ‘Faced with the possible dismissal of nursing professionals due to the salary floor, how would you, as a leader, address this issue to keep the team motivated and engaged?’; ‘Faced with signs of stress in the team, how would you promote an organizational culture that effectively addresses work overload and preserves the well-being of professionals? ‘; ‘In an environment where conflicts can arise due to difficult ethical decisions, as a leader, how would you mediate a conflict between team members with opposing views on the allocation of scarce resources?’; ‘As a leader, how would you provide constructive feedback to team members who have made medication errors, while promoting professional development?’; ‘How do you conceptualize leadership?’; ‘Do you consider yourself a leader?’; ‘Tick the interpersonal skills you consider necessary for a leader?’

QUAPEEL is a questionnaire that measures the skills and attitudes that nurses should exercise in their leadership practice. For use in this study, the questionnaire will be adapted in the section referring to the sociodemographic question, since the instrument will be applied to students and not to nurses.

The application of QUAPEEL involves three main parts: the first part collects sociodemographic information about the interviewees, such as age, education and professional experience; the second part consists of questions that explore nurses’ knowledge about leadership, allowing for a qualitative and quantitative assessment; and the third part focuses on specific leadership competencies, addressing skills and attitudes that nurses believe they possess or need to develop.

The third part of the questionnaire consists of 20 statements that assess the dimensions of the coaching process, with each dimension having six specific situations. For each statement, there are the following alternatives: “1. Never” - I don’t understand the statement; “2. Rarely” - I understand the statement sometimes; “3. Not always” - I understand the statement sometimes; “4. Almost always” - I understand the statement many times; “5. Always” - I understand the statement all the time; “NA. Not applicable” - if you have no way of evaluating the question. The instrument’s score ranges from 0 to 100, with values closer to 0 corresponding to the lowest perception and values closer to 100 to the highest perception of Leadership practice.

These instruments will allow for both quantitative and qualitative assessment, as well as addressing the skills and attitudes that students believe they possess or need to develop. This format ensures that both the control and experimental groups will have access to the same data collection instruments, promoting equality in the evaluation conditions.

Fig 1 shows the detailed stages of the study, with SPIRIT enrollment timeline, interventions and assessments.

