### Data analysis

The results analyzed will be related to the evaluation of the effectiveness of the online educational module in the acquisition of knowledge about Leadership among Nursing students, and this effectiveness will be measured by means of a pre-test and a post-test, using a problem situation instrument and the QUAPEEL questionnaire.

Therefore, in addition to the age and gender of the participants, the variables to be analyzed will include the responses of the control and experimental groups, obtained by applying the instrument containing the problem situation and the *QUAPEEL* questionnaire (S4).

The collected data will be stored and processed using Microsoft Office Excel, version 2020, and Statistical Package for the Social Sciences (SPSS), version 25.0. The analysis will include both descriptive and inferential statistics, with results presented in tables and figures.

Descriptive data treatment will involve analyzing relative and absolute frequencies, mean, standard deviation, and medians according to the normality of the variables. The normality of the data distribution will be checked using appropriate statistical tests, such as the Shapiro-Wilk test or the Kolmogorov-Smirnov test.

The answers will be analyzed using the content analysis technique and the use of a frequency scale, ranging from “Never” to “Always”, aims to measure the participants’ self-perception in relation to the frequency with which they apply leadership practices in their daily lives. This approach is essential for assessing not only the presence of such practices, but also the consistency with which they are used in different scenarios. Although the focus is on frequency, the interpretation of the data allows inferences to be made about the participants’ understanding and use of leadership practices, in line with the objectives of the study.

To analyze the pre-test and post-test conditions of the study in this protocol, the tests to be used will depend on the distribution of the data. If the data is normally distributed, the Student’s t-test for paired samples will be used to compare the means of the two moments and check for statistically significant differences.

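### The QUAPEEL response options are labelled as frequencies but defined as understanding of the statement, while the score is to be read as self-perceived leadership practice

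*Protocol article*

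**What the plan says.** The Data collection instrument section describes the scored part of QUAPEEL: "The third part of the questionnaire consists of 20 statements". Each statement has five numbered options plus a not-applicable option. Every numbered option joins a frequency label to a definition, and all five definitions concern comprehension. The lowest is "1. Never” - I don’t understand the statement" and the highest is "5. Always” - I understand the statement all the time". Options 2 and 3 have the same definition: "2. Rarely” - I understand the statement sometimes" and "3. Not always” - I understand the statement sometimes".

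The same section gives the total a range of 0 to 100, with "values closer to 100 to the highest perception of Leadership practice". The Data analysis section says the Never-to-Always scale is meant to measure "self-perception in relation to the frequency with which they apply leadership practices in their daily lives". It adds that understanding and use may be inferred from the answers, but keeps frequency as the main interest. The Secondary outcome section assigns the questionnaire to the secondary outcome and calls that outcome knowledge acquisition.

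**The concern.** A response option should put one question to the student. Here the label asks how often the practice is carried out, and the definition asks how well the sentence is understood. A student can understand a statement completely and never act on it. That student belongs in category 5 by the definition and category 1 by the label, and the article does not say which governs.

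What is at stake is the meaning of the secondary score. A leadership course can be expected to improve comprehension of sentences about leadership. If students answer by the definitions, that improvement enters the pre-to-post change and would be reported as more frequent self-perceived practice. If some students change from one reading to the other between tests, the change contains an artefact that cannot be removed afterwards, because nothing records which reading a student used.

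**Working it through.** **Inputs.** From the Data collection instrument section: 20 statements, options coded 1 to 5, stated range 0 to 100. From the Data analysis section: the score is read as frequency of practice, and pre and post are compared by a paired t-test or a Wilcoxon test. The student profiles below are assumptions.

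**The plan's own figure.** A plain sum runs from 20 × 1 = 20 to 20 × 5 = 100, so the stated minimum of 0 is not reproduced. Rescaling by (raw − 20) / 80 × 100 gives 0 to 100, and so does coding not-applicable as 0. The article states neither rule. The plain sum is used below, with rescaled values in brackets.

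**Comparison of the texts.** All five definitions have understanding as their subject; none mentions doing anything. The Data analysis text treats understanding as something inferred from frequency answers. The option definitions make it the answer itself. The two are not reconciled.

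**One occasion.** A student understands all 20 statements and practises none.
- By definition: 20 × 5 = 100 [100].
- By label: 20 × 1 = 20 [0].
- Gap: 80 [100] points. This is the largest possible.

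**Change when comprehension rises and practice does not.** A student follows the definitions. At pre-test, 10 statements are understood fully and 10 sometimes; at post-test, all 20 are understood fully. Practice is rare (2) both times.
- By definition, sometimes coded 3: 10 × 5 + 10 × 3 = 80, then 100. Change +20 [+25].
- By definition, sometimes coded 2, which the shared wording equally allows: 10 × 5 + 10 × 2 = 70, then 100. Change +30 [+37.5].
- By label: 20 × 2 = 40, then 40. Change 0.

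More generally, a one-category rise in understanding on 5, 10 or 20 items adds 5, 10 or 20 raw points [6.25, 12.5 or 25] with practice unchanged.

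**Constant reading.** If a student uses the same reading at both tests, the level difference between the readings is in both scores and drops out of post minus pre. What remains is true change in whichever construct that student was rating.

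**Change of reading.** If a share p of students moves from label to definition between tests, and D is the gap between readings, the artefact in the mean change is p × D. Assume mean item scores of 4.5 by definition and 2.5 by label, so D = 20 × (4.5 − 2.5) = 40. Then p = 0.10 gives 4 points and p = 0.25 gives 10. Movement the other way gives the same figures with a negative sign. Neither p nor D can be obtained from the document.

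**The case against.** The strongest reply is that the wording students will see is unknown. The form is S4, which is not shown. The article announces adaptation of the sociodemographic section only, and its description is in English for a Brazilian study. The identical definitions of options 2 and 3 suggest rough translation. Students may see the labels alone or sound Portuguese wording. This stands, and it makes the consequence conditional. It does not remove the contradiction: the article presents these texts as the alternatives offered for each statement.

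A second reply is that the Data analysis section already settles the intended reading as frequency. That shows what the investigators mean, not what a student would answer from the definitions as written.

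A third is that the secondary outcome is called knowledge acquisition, so a rise in understanding is closer to it than practice is. That has some force, but understanding a questionnaire sentence is not the construct the score is said to measure. The reply mainly shows that the outcome section needs aligning too.

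A reader might go further in three ways that the document does not support:
- **That the arms will be compared with bias.** Both arms complete the same form. Distortion between arms needs a different gain in comprehension or different switching. The Discussion describes different materials in the two arms, so this cannot be ruled out, but it is not shown.
- **That mixed readings will inflate the variance of the planned analysis.** The tests named are paired, and a constant reading adds no offset to the change.
- **That the primary outcome is affected.** The Primary outcome section does mention QUAPEEL, but it first assigns that outcome to the problem situation instrument. This is a separate inconsistency, and reach into the primary result is speculative.

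**Conclusion.** The point holds as a contradiction in the response rule. As described, the options score comprehension of the statement, while the total is to be reported as self-perceived leadership practice. This goes beyond wording, because answers given as written would measure a different construct.

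The conclusion about the data is conditional on the form showing these definitions. For one student the two readings can differ by up to 80 points on a plain 20-item sum. The effect on the mean paired change is unknown; the 4 and 10 points above are illustrations resting on assumed item means and switching shares. It cannot be concluded from the document that the administered score will be wrong. The matter should be settled before the pre-test, since it cannot be repaired afterwards.

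**What to change.** The Study situation section says recruitment is still being prepared, so this can be done before the pre-test opens:

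1. Check the option wording in the Data collection instrument section and in S4 against the source instrument.
2. Make the five definitions state frequency of practice, consistent with the labels and the Data analysis section, or show the labels only. Give options 2 and 3 distinct meanings.
3. Use identical wording at pre-test and post-test.
4. If understanding is also wanted, ask it as a separate item and keep it out of the QUAPEEL total.
5. State in the Secondary outcome section which construct the score represents.

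If S4 already carries only frequency wording, no change to the form is needed on this point and it is enough to correct the article.

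The cost is a short wording change and a minor ethics notification, with no added participants or procedures. If the final wording departs from the published instrument, some comparability with it is lost, which is why the source should be checked before anything is rewritten.

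### The QUAPEEL score is described inconsistently: a plain sum of 20 items coded 1 to 5 runs from 20 to 100, not 0 to 100, and two response options share one definition

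*Protocol article*

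**What the plan says.** All of this comes from the protocol article.

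- **Items and dimensions** (Data collection instrument): the third part of QUAPEEL "consists of 20 statements that assess the dimensions of the coaching process, with each dimension having six specific situations".
- **Response options** (same section): five options coded 1 to 5, each with an explanation, plus an NA option for a statement that the respondent cannot evaluate. NA is given no numeric value. The first option reads "1. Never” - I don’t understand the statement". Options 2 (*Rarely*) and 3 (*Not always*) are both explained as "I understand the statement sometimes".
- **Score** (same section): the "score ranges from 0 to 100, with values closer to 0 corresponding to the lowest perception"; values near 100 mean the highest perception. The section does not say whether the score is a sum, a rescaled sum or a mean.
- **Adaptation** (same section): only the sociodemographic section is to be changed, "since the instrument will be applied to students and not to nurses".
- **Interpretation** (Data analysis): the scale is meant to capture "self-perception in relation to the frequency with which they apply leadership practices in their daily lives".
- **Role**: Secondary outcome rests on this questionnaire. Primary outcome also names it as the measure of the primary concepts, after first naming the problem-situation instrument.

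**The concern.** The item count, codes and range given in one section do not fit together under the simplest scoring rule. Either the range is misreported, or the article leaves unsaid a rescaling or a value for NA.

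The response wording matters more, because it acts when the student answers. If the form carries these explanations, two scored categories are blurred and students are asked about comprehension when the analysis wants frequency of practice. No later scoring rule can repair that.

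NA is a conditional risk. If it pulls the total down, a student who becomes able to judge more statements after a course would appear to gain in self-perception with no rated item changed. The planned tests are paired comparisons of pre-test and post-test, which is where such a change would show.

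**Working it through.** **Inputs** (Data collection instrument): 20 statements; lowest code 1; highest code 5; NA without a value; six situations per dimension; stated range 0 to 100.

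**1. Reproducing the stated range**

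| Scoring rule | Minimum | Maximum | Gives 0–100? |
|---|---|---|---|
| Plain sum, all items rated | 20 × 1 = 20 | 20 × 5 = 100 | No |
| Percentage of maximum | 100 × 20/100 = 20 | 100 × 100/100 = 100 | No |
| Sum with NA = 0 | 0 (all 20 items NA) | 100 | Yes |
| Rescaled sum, 100 × (sum − 20)/80 | 100 × 0/80 = 0 | 100 × 80/80 = 100 | Yes |
| Rescaled mean, 100 × (mean of answered items − 1)/4 | 100 × 0/4 = 0 | 100 × 4/4 = 100 | Yes |

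The upper bound reproduces under every rule. The lower bound does not reproduce from a plain sum. Three rules give 0, and the article states none of them.

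**2. Meaning of 0 if NA counts as zero.** Twenty NA answers score 0 and twenty *Never* answers score 20. The bottom of the scale would then mean that nothing could be judged, which conflicts with the article's reading of low values as lowest perception.

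**3. Effect of NA on the total, under a condition.** Assume that NA adds zero, or is dropped from a sum that is not prorated. Each NA then removes the code it replaces, between 1 and 5 points. For a student who rates every answered item 4, with k NA answers, the total is 4 × (20 − k):

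| k | Sum, NA adds nothing | Prorated sum | Rescaled mean of answered items |
|---|---|---|---|
| 0 | 80 | 80 | 75 |
| 3 | 68 | 80 | 75 |
| 5 | 60 | 80 | 75 |

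Going from three NA answers at pre-test to none at post-test would add 80 − 68 = 12 points under the first rule and nothing under the other two. The last two columns are constant because every answered item has the same rating. With mixed ratings, a mean over answered items can still shift with which items are skipped, but it has no built-in penalty for NA.

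**4. Response definitions.** Codes 2 and 3 differ by 1 point on the raw sum, or 100 × 1/80 = 1.25 points on the rescaled sum, for each item. Their explanations are the same, so only the labels separate them.

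**5. Construct.** All five explanations, from not understanding to understanding all the time, concern comprehension of the statement. Data analysis reads the same answers as how often leadership practices are applied. A student can understand a statement fully and never do what it describes.

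**6. Dimensions.** 20/6 = 3.33. Three dimensions of six need 18 items and four need 24.

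**The case against.** Several arguments on the other side have force.

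- **The article never says the score is a plain sum.** A linear rescaling of the same items and codes gives exactly 0 to 100. This stands. A reader might infer that a 0–100 score cannot come from these items; the text does not support that.
- **NA has no stated value.** A reader might infer that the score falls with every NA. That holds only under the assumption in step 3, so the 68, 60 and 12-point figures are illustrations and not estimates for this trial. This stands.
- **Scoring rules and NA handling often sit in the instrument's own documentation, a supplement or an analysis plan**, and none of these is shown. Their absence from an article is no fault. This stands. The point here is what the article does state and how its statements conflict.
- **Frequent use of NA by students is speculative.** Adapting only the sociodemographic section makes it conceivable, but no rate is given. This stands. A drift common to both arms would also tend to cancel between arms, so a spurious arm difference is not shown. It would not cancel in the paired pre-post tests that Data analysis names.
- **The labels and codes of options 2 and 3 differ, and the shared explanation may be a translation slip.** This stands in part. The categories are blurred rather than indistinguishable, and the form that students will see is not shown. If the form repeats the article's wording, the ambiguity is real.
- **Data analysis does discuss understanding**, saying that it can be inferred from frequency. That does not resolve the mismatch, because the explanations do not ask about frequency; only the labels do.

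**Conclusion.** The point holds as an internal inconsistency in the description of the secondary measure, and it should be corrected before the pre-test. Four parts rest on the text alone:

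- the stated floor of 0 does not match a plain sum, whose floor is 20;
- options 2 and 3 carry one definition;
- the definitions ask about understanding while the analysis is of frequency;
- 20 statements do not divide into dimensions of six.

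The NA effect is conditional. It is 1 to 5 points per NA if NA counts as zero or is dropped from an unprorated sum. A prorated sum or a mean of answered items carries no automatic penalty.

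A reader might go further and conclude that the secondary score is wrong or biased by 12 points. The documents do not support that: they fix neither the scoring formula nor a value for NA, and they give no NA frequency. What is shown is that the score cannot be reproduced from the article, and that the response wording, if used as printed, would weaken what it measures.

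**What to change.** Before the pre-test, in Data collection instrument and on the form:

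1. Give options 2 and 3 distinct definitions, and word all five as frequency of practice, in line with Data analysis and checked against the source instrument.
2. State the scoring formula and make the range match it: 20 to 100 for a sum, or 0 to 100 for 100 × (mean of answered items − 1)/4.
3. Treat NA as missing, not as zero, and report the number of NA answers by arm and time point.
4. Reconcile the 20 statements with the six situations per dimension.

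The cost is form wording and one scoring line. Study situation says that recruitment is still being prepared, so no data need be rescored. The downside is that a rescaled score is not directly comparable with published sums; reporting the raw sum alongside it deals with this.

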**Fig 1 pone.0320208.g001:**
[figure not shown]
Description of the study stages.

### Blinding

The single-blind design was adopted to ensure data integrity and minimize biases. Participants will be informed on the registration form about the general differences between the two teaching modalities. However, the specific allocation of participants to each group will be conducted confidentially and randomly to avoid external interference and reduce bias. This approach guarantees transparency with the participants while maintaining the impartiality necessary for the validity of the study.

The researcher teaching the in person course for the control group will necessarily know the participants in this condition. However, to mitigate any potential bias arising from this limitation, the statistician responsible for processing the data will not know which group each participant will be in, so that the analysis of the data is not influenced during or after the study, until the final analyses have been completed. To ensure impartiality in data handling, the data were presented without any identification that would reveal to which group each participant belonged.

